### Participants and Selection Criteria

According to data extracted from the Basque Statistics Institute (EUSTAT) [19], as of October 16, 2020, the reference population to extract the sample residents in the BAC, aged between 6 and 17 years (born between 2003 and 2014), is 254,093 people, of whom 130,645 are boys and 123,448 are girls.

The corresponding sample size, considering that we are referencing a universal population greater than 100,000 people (referred as infinite for sample size calculation) is 1111 participants, at a confidence level of 2σ of 95.5%, an error limit of 3%, and heterogeneity of 50% [20]. To ensure a proportionate distribution of the sample in all age groups, territories, public and private centers, as well as girls and boys, these 1111 people were selected in accordance with the distribution detailed in Table 1. This sample is defined for all the assessment tests that comprise the project.

There is a proportional and random stratification based on province and county, age, gender, education network (public or private), and medea (socioeconomic level based on the deprivation index per census section, which enables the identification of sections with socioeconomic conditions), along with some inclusion and exclusion criteria that are listed in Textbox 1. Schools were selected randomly on the basis of the above-mentioned criteria.

**Table 1 table1:** Sample size and the current sample (N=1111).

Grade	Araba province				Bizkaia province				Gipuzkoa province				Total			
	Male		Female		Male		Female		Male		Female		Male		Female	
	Sample, n	Current sample, n	Sample, n	Current sample, n	Sample, n	Current sample, n	Sample, n	Current sample, n	Sample, n	Current sample, n	Sample, n	Current sample, n	Sample, n	Current sample, n	Sample, n	Current sample, n
First primary	8	9	7	8	22	6	21	6	14	1	14	1	44	16	43	15
Second primary	7	8	7	8	22	5	21	5	15	1	14	1	44	14	42	14
Third primary	8	8	7	7	23	5	22	5	16	1	15	1	48	14	44	13
Fourth primary	8	8	8	8	24	6	23	6	16	1	16	1	48	15	47	15
Fifth primary	8	6	8	7	24	6	23	6	17	0	16	1	49	12	47	14
Sixth primary	8	6	7	6	24	6	23	8	17	1	16	0	49	13	45	14
First secondary	8	7	7	6	25	4	24	5	17	0	16	1	50	11	47	12
Second secondary	7	6	7	6	25	4	22	5	17	1	16	0	48	11	46	11
Third secondary	7	8	7	7	24	4	22	10	17	0	16	1	48	12	45	18
Fourth secondary	7	8	7	8	24	10	23	8	17	1	16	0	47	19	45	16
First high school	7	8	7	7	24	8	23	14	16	1	16	1	48	17	45	22
Second high school	7	8	7	7	24	3	22	3	17	1	15	1	48	12	44	11

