**Exclusion criteria:**
Nonconsent or refusal by the child or adolescent to complete the physical activity diary or use the accelerometer, even with signed informed consent by their parents or legal guardiansPhysical or intellectual disability that prevents completing the daily physical activity or use of the accelerometer in accordance with the defined protocol. Each case will be assessed with each school’s teaching team and with the parents or legal guardians of the minor

To reach 1111 individuals, the sample unit selection will be conducted in multiple stages, so that a random sample of all age strata will be obtained, and a subsequent selection (by randomization) will be made to meet the needs of age, gender, and type of established center for the project. The recruitment process can be divided into three phases: contact with the center, contact with the families, and contact with the students. The contact with the centers is initiated via email or a telephone call. If the school shows interest, we arrange a meeting with the school’s principal. The principal selects a person from the school who then becomes the person in charge of the selection process and sending the information to the parents, usually the physical education teacher. Depending on the requirements of the total sample, the age ranges that need to be covered in each school are selected. During this phase, the physical education teachers of each center will be contacted, as well as the counselors for each grade level to request their collaboration and thus carry out an initial preselection of students to participate in the study (Figure 1). The information and the documents to be filled out are sent to the parents. A lottery is held among the participants who meet the requirements (age, gender, and others) and whose parents have given their consent. If the principal, the physical education teacher, the participants, or their parents have queries about the study, they are clarified. A day is set for placing the accelerometers on the selected participants, and after 7 full days they are removed.

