### Data Collection

Each participant will be identified by a unique and confidential numerical code, which is assigned after informed consent is obtained from the legal guardians. Those responsible for the database must save the files on servers with a password. To determine the codes, the following process is followed:

Province: 1=Araba, 2=Bizkaia, and 3=Gipuzkoa.Town (000)—each town is assigned a 3-digit number (eg, 001, 002, etc)Education center is assigned a 3-digit number (eg, 001, 002, etc).The academic stage between primary, secondary, or high school or secondary vocational training (1, 2, and 3)The gradeThe classroom in letters A, B, C, and DThe student number (00) considering that each classroom will have a maximum of 30 students.

Consequently, each participant will have a 12-digit code; for example, 2 022 060 11 D 07.

Prior to data collection, the study presentation brochure was emailed to the centers inviting them to participate, along with the informed consent document to authorize their children to participate in the study. Each center shares information about the study with the families through the established communication channel in each case (web platform or email), sending the legal guardians the information received at the center.

If families are interested in participating, they must send their informed consent to the head of the education center, and depending on the number of volunteers, a random draw will be held until the sample requirements established in each area and center are reached.

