### Statistical Analysis

The statistical analysis will be performed using SPSS (version 27.0.1.0; IBM Corp). Parametric tests will be performed after all assumptions for each test are met. For comparison between groups (girls vs boys, age groups, school types, and regions) 2-tailed *t* tests, 1-way analysis of variance, or the nonparametric method of Kruskal-Wallis and chi-square tests will be used for the main primary outcomes as dependent variables.

Descriptive statistics will be used for all outcome variables, and the effect size and the level of significance corresponding to the main group (between participants) will be reported. To prevent a type I error, post hoc comparison will be performed when a significant interaction effect is present. Values will be expressed as mean (SD). The significance level will be set at 95% (α=.05).

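### School-type and region comparisons use tests that assume independent pupils, although pupils are drawn within schools, so their type I error exceeds 5% whenever outcomes correlate within school.

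*Protocol article*

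**What the plan says.** **Sampling.** Under Participants and Selection Criteria the article states "Schools were selected randomly on the basis of the above-mentioned criteria". After the exclusion criteria it adds that "the sample unit selection will be conducted in multiple stages". Data Collection describes the last stage: among consenting families, "a random draw will be held until the sample requirements established in each area and center are reached". Stratification is by province and county, age, gender, education network and MEDEA (the deprivation index).

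**Analysis.** The Statistical Analysis section introduces the tests with "For comparison between groups (girls vs boys, age groups, school types, and regions". It then names two-tailed t tests, followed by "1-way analysis of variance, or the nonparametric method of Kruskal-Wallis and chi-square tests will be used for the main primary outcomes as dependent variables". The level is α = .05. On assumptions it says only: "Parametric tests will be performed after all assumptions for each test are met". The section names no school term, cluster-robust variance or survey method.

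**The concern.** Pupils in one school share a timetable, physical education provision, recess, school sport and neighborhood. Study Variables lists several of these as settings in which activity is measured, so some correlation within schools is to be expected. A test that ignores it treats each pupil as a separate piece of evidence.

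For a factor that is constant within a school, such as public versus private or province, this makes the standard error too small and the nominal 5% too low. Chance differences between schools would then be reported too often as differences between school types or provinces. The Discussion intends the results to guide action by education and health departments, so such findings could be acted on.

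**Working it through.** **Inputs from the article**
- Two-sided α = .05; tests as named (Statistical Analysis).
- Two school types, public and private; three provinces with targets of 175, 554 and 382 (Results).
- Two-stage draw, schools and then pupils (Participants and Selection Criteria; Data Collection).

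**Inputs not in the article, assumed here**
- Pupils per school, m: 5 to 20 in the table below.
- ICC: .01 to .10.

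**The plan's own figure.** The sample size is z²p(1−p)/e² = 2² × 0.5 × 0.5 / 0.03² = 1111.1, which reproduces 1111. This is the simple-random-sampling formula, with a design effect of 1. The planning figure makes the same independence assumption as the tests.

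**Formulas.** For a factor constant within schools of equal size:
- DEFF = 1 + (m − 1) × ICC
- Two groups (school type): actual α = 2 × [1 − Φ(1.96/√DEFF)]
- Three groups (regions): actual α = P(χ² on 2 df > 5.991/DEFF)

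**Worked case, m = 20, ICC .05.** DEFF = 1 + 19 × 0.05 = 1.95. For school type, 1.96/√1.95 = 1.404, giving 16.0%. For regions, 5.991/1.95 = 3.07, giving 21.5%.

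| m | ICC | DEFF | School type | Three regions |
|---|---|---|---|---|
| 5 | .01 | 1.04 | 5.5% | 5.6% |
| 10 | .01 | 1.09 | 6.0% | 6.4% |
| 10 | .05 | 1.45 | 10.4% | 12.7% |
| 20 | .05 | 1.95 | 16.0% | 21.5% |
| 20 | .10 | 2.90 | 25.0% | 35.6% |

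**Check by simulation.** With no true difference, 2,000 runs, m = 20, ICC .05, 56 equal schools and province sizes close to the targets, the rejection rates were:
- t test by school type: 15.4%
- ANOVA by region: 21.5%
- Kruskal-Wallis by region: 20.7%
- chi-square by school type, outcome split at its mean: 12.5%
- t test between two halves of each school, standing in for girls versus boys: 4.8%

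Moving from ANOVA to Kruskal-Wallis changes almost nothing. The chi-square rate is lower than the t test rate but still well over 5% in this setting.

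**Age.** The recruitment text says that the age ranges to be covered are chosen school by school. Age is therefore partly a between-school factor, and some inflation follows. The article gives no basis for putting a number on it.

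**The case against.** **The assumption check.** It could be said that the promise to verify assumptions covers independence. It does not help: it governs parametric tests only, and the named fallbacks need independence too. The section also mentions a significant interaction effect, which suggests some multi-factor analysis. None is named, and an interaction term between pupil or school characteristics would not account for school.

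**A condensed article.** A fuller analysis plan may exist. Omitted detail would not be a fault, but here the tests are named, and they do not fit the sampling that the same article describes.

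**Size.** A reader might infer that false-positive rates will be well above 5%. The article does not support that as a statement of fact. With few pupils per school and a low ICC the rate is 5.5% to 6.4%, and stratification may absorb part of the between-school variance. This objection stands: the direction is certain for a positive ICC, the amount is not.

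**Other readings that go too far**
- *That only the number of schools carries information.* This holds only as the ICC approaches 1. At m = 20, ICC .05, the effective sample is 1111/1.95 ≈ 570, against 1111/20 ≈ 56 schools.
- *That the sex comparison is seriously harmed.* For a within-school contrast the naive standard error is too large by a factor of 1/√(1 − ICC), which is 2.6% at ICC .05 and 5.4% at ICC .10. That is slight and conservative.
- *That school type must be adjusted for deprivation.* The main objective is descriptive, and an unadjusted public/private difference is a legitimate quantity. Adjustment is a choice of question.
- *That rank tests must be abandoned.* Cluster-adjusted rank tests exist; the problem lies with the standard version named.

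**Importance.** The hypotheses in the Introduction concern compliance with the WHO recommendation and boys versus girls, not school type or region. That is fair. Still, school type and region are two of the four comparisons planned for the main primary outcomes. Age, where the Discussion expects significant differences, is a third that may be partly affected.

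**Conclusion.** The point holds in a conditional form. The named tests do not match the two-stage sampling, and nothing else in the article repairs this. For school type and region, the actual type I error is above the stated 5% for any positive ICC.

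The excess depends on two quantities that the article does not give. Over the assumed values in the table it runs from negligible (5.5% and 5.6%) to large (25% and 36%). It reaches about 10% or more once the ICC is about .05 with 10 or more pupils per school. These figures assume equal school sizes and no gain from stratification. Age comparisons share the problem in part, to an unknown degree; the within-school sex comparison does not.

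**What to change.** Amend the Statistical Analysis section, before analysis, so that all group comparisons account for school. Either of two approaches serves:

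- a linear mixed model (minutes of activity, sedentary time, sleep) or a logistic mixed model (meeting the WHO recommendation), with a random intercept for school; or
- a complex-survey analysis with school as the primary sampling unit and the sampling strata declared: province and county, age, gender, network and MEDEA.

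In both, the degrees of freedom should reflect the number of schools. A cluster-adjusted rank test is acceptable for skewed outcomes. The choice should be fixed in advance, because a mixed logistic model and a survey analysis estimate different quantities. A school-type comparison adjusted for MEDEA may be reported beside the unadjusted one.

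The cost is revised wording and slightly more analysis work. No new data are needed, since Data Collection already puts the center code in the participant identifier. The downside is wider intervals for school type and region.

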**Results:**

The results of this study intend to demonstrate significant differences in PA levels in different age and gender groups since the volume of school PA in the BAC decreases as the age of the schoolchildren increases. The total study sample includes 1111 participants. In April 2021, up to 50% of the sample size was reached, which is expected to increase to 100% by April 2022. This sample will allow us to analyze, discuss, compare, and assess the reality of the school population, in a sensitive period of adherence to behavior patterns, using data from the geographical and administrative area of the BAC. This study will provide a realistic insight into PA levels among children and adolescents in the BAC. It will also offer scientific contributions on the positive relationship between PA levels and sleep quality in this population.

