Interventions promoting PA among children and adolescents must be supported by evidence that provides us the necessary information to do so efficiently. This study will allow us to analyze different realities (at different times, school settings, and ages), ultimately facilitating the design of policies and programs to promote PA and health on the basis of stated evidence [15]. Moreover, in the Basque Autonomous Community (BAC), there is a lack of evidence regarding the level of PA among children [16].

To determine the level of PA in the school population aged between 6 and 17 years in the BAC, and considering the benefits of PA for children and adolescents [17,18], this protocol aims to determine whether this group meets the established parameters of daily PA recommended by the WHO [2]. We hypothesize that >50% of the children do not meet the WHO recommendations, and that the level of PA in boys is greater than that in girls.

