## Discussion

### Expected Findings

This study aims to provide current estimates of the levels of PA, sedentary behavior, and sleep among children and adolescents in the BAC (6-17 years old). Sedentary behavior is fundamentally important in the health of children and adolescents [29], and it is highly influenced by the social environment in which they live [30]. Recent statistics show that 28% of children in Spain between the ages of 3 and 8 years are overweight, and 9% are obese [31]. It is clear that increased PA and reducing sedentary behavior play a leading role in preventing overweight and excess adiposity, even when people present an adverse genetic condition that predisposes them to be obese [32]. Some studies seem to have shown an inverse relationship between MVPA with adiposity and cardiometabolic risk, and a positive relationship between MVPA with cardiorespiratory fitness and total body bone mineral density among children and adolescents [33]. Other studies maintain that screen time has a significant and inverse relationship with hours of sleep, unregulated activity (games and other activities), and physical exercise [34].

The results of this study intend to demonstrate significant differences in PA levels in different age groups since the volume of school PA in the BAC decreases as the age of the schoolchildren increases. In terms of gender, it is higher among boys than in girls, reaching the same conclusions as other authors [35,36].

The results will be used to analyze and assess the relevance of creating a battery of assessment of physical condition in the Basque Government (interdepartmental) as an improvement in the diagnosis of the state of physical condition and to be able to intervene from the department of education and the department of health to address, together with the Directorate of Physical Activity and Sport the concrete actions to be developed as process improvement and move in an improvement of physical conditions in future evaluations.

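### Age groups are compared only with tests that ignore order, although the age difference is expected because school activity falls with age; a prespecified trend estimate should be added beside them.

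*Protocol article*

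**What the plan says.** The Statistical Analysis section lists the comparisons as "girls vs boys, age groups, school types, and regions". Besides two-tailed t tests it names "1-way analysis of variance, or the nonparametric method of Kruskal-Wallis and chi-square tests will be used for the main primary outcomes". The level is α=.05. On follow-up it says that "post hoc comparison will be performed when a significant interaction effect is present". Descriptive statistics, means with SDs and effect sizes will be reported. It names no trend test, ordered contrast or regression on age.

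The Abstract (Results) expects differences by age and gender "since the volume of school PA in the BAC decreases as the age of the schoolchildren increases". Expected Findings in the Discussion repeats this for age: "The results of this study intend to demonstrate significant differences in PA levels in different age groups since the volume of school PA" is said to fall as age rises.

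The formal hypotheses, at the end of the Background, do not mention age: "We hypothesize that >50% of the children do not meet the WHO recommendations, and that the level of PA in boys is greater than that", the comparison being with girls. The main objective is descriptive.

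**The concern.** The reason given for the age difference has an order and a direction: older children get less school PA. One-way ANOVA, Kruskal-Wallis and the ordinary chi-square test treat age groups as unordered labels. Shuffling the labels leaves the p-value unchanged, so a rise with age, or one unusual grade, can reject as readily as a steady fall.

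The follow-up rule does not repair this. A one-way layout has no interaction term, so read literally a significant age effect triggers no planned comparison.

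At stake is one of the group findings that the article says it intends to demonstrate. A significant omnibus result could be reported as a fall with age that was never tested, and a modest steady fall could be missed although a trend test would have found it.

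**Working it through.** **Inputs from the article.** α = 0.05. Table 1 target totals by grade (boys plus girls), first primary to second high school: 87, 86, 92, 95, 96, 94, 97, 94, 93, 92, 93, 92; sum 1111. By school stage: primary 550, secondary 376, high school 185.

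**Assumptions (not in the article).** Two-sided trend test, 80% power unless stated, independent observations, equal SD, and a straight-line fall over the 12 grades. The number of age groups k is not fixed. The range 3 (the stages in the participant code) to 12 (the grades in Table 1) is used.

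**1. The article's own figure.** n = z²p(1−p)/e² = 2² × 0.25 / 0.03² = 1111.1, which reproduces 1111. It is the precision of one proportion and involves no age comparison.

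**2. Noncentrality under a linear fall.** For a total fall of D standard deviations from first to last grade, λ = N × Var(grade/11) × D². With grades scored 0 to 11 and weighted by Table 1, Var(grade) = 11.65, so Var(grade/11) = 11.65/121 = 0.0963. Collapsing to three stages leaves a between-stage variance of 9.75, and 9.75/11.65 = 0.837 of λ is kept.

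**3. Power at equal effect.** A 1-df trend test has 80% power at λ = 7.86, so D = √(7.86 / (1111 × 0.0963)) = 0.27. For that fall, by the noncentral F:
- 12-grade ANOVA (11 df, λ = 7.86): 41%
- three-stage ANOVA (2 df, λ = 0.837 × 7.86 = 6.58): 63%

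**4. Sample ratio, omnibus to trend, for 80% power.**
- Three stages, trend on the same three groups: 9.66/7.86 = 1.23
- Three stages, trend on single grades: 1.23/0.837 = 1.47
- Twelve grades: 16.95/7.86 = 2.16 (2.14 with the large-sample chi-square)

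Between these, on the same groups, the chi-square ratio is 1.39 for 4 groups, 1.63 for 6 and 1.83 for 8.

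**5. Larger linear falls at N=1111.**

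| Fall, first to last grade | Trend | Three-stage ANOVA | 12-grade ANOVA |
|---|---|---|---|
| 0.30 SD | 87% | 72% | 50% |
| 0.40 SD | 98–99% | 93% | 80% |

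**6. Falls that come in steps.** Same sizes and assumptions, except that PA drops once and stays down.

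| Pattern | Trend | Three-stage ANOVA | 12-grade ANOVA |
|---|---|---|---|
| 0.30 SD drop at high school only | 67% | 93% | 69% |
| 0.20 SD drop at entry to secondary | 82% | 86% | 57% |

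In both patterns PA truly falls with age, yet the three-stage ANOVA has more power than the linear trend.

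**The case against.** The strongest reply is that the article never hypothesizes a decline of PA with age. Its two hypotheses concern WHO compliance and sex. The fall in school PA is offered as a reason, and what is to be shown is differences between age groups, which an omnibus test does address. This stands. A reader might infer that a formal ordered hypothesis is being tested with the wrong test; the text does not support that.

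Second, the reported group means will show the direction. This also stands: it is too strong to say that the planned analysis cannot show a decline. What is missing is a planned test or interval for it.

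Third, the size of the loss rests on inputs that the article does not give. Twelve groups are nowhere stated as the plan. With three groups and a trend on those same groups the ratio is only 1.23, and the 1.47 adds the loss from collapsing grades. For a linear fall of 0.40 SD even the 12-grade ANOVA has 80% power.

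Fourth, the trend test is not uniformly better, as the step patterns show. This is the most important limit, and it rules out replacing or demoting the omnibus test.

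Fifth, ordered contrasts might sit in a fuller analysis plan. That is possible, but the article does commit to a family of tests and to a post hoc rule, and that rule does not fit one-way tests.

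**Conclusion.** The point holds as a gap between the stated reason for the age difference and the tests named for it. The named tests for three or more age groups ignore order, and the post hoc rule depends on a term that they do not contain. The omnibus p-value alone cannot establish a decline.

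The efficiency cost is about 1.2 to 2.2 times the sample of a 1-df trend test. It assumes a near-linear decline, 3 to 12 groups, 80% power and independent observations; the ratios do not depend on the SD. For stepwise declines the advantage can reverse.

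A reader might infer that 1111 is too small by this factor. It is not shown to be: the number was set by the precision of one proportion, for a study whose main objective is descriptive. The omnibus tests are valid for the question whether age groups differ. The plan should be changed because the addition is cheap and answers the age question directly.

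**What to change.** In the Statistical Analysis section:
- Prespecify a linear trend over grade or exact age for the activity outcomes, reported as change per year with a 95% CI. Use a logistic trend for meeting the WHO recommendation, and Jonckheere-Terpstra if ranks are used.
- Keep the omnibus age-group test alongside it, with equal standing, and state the age groups.
- Trigger post hoc age comparisons on a significant age main effect instead of an interaction.

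The cost is a few sentences. Grade is a listed study variable and date of birth is recorded when the accelerometer is programmed, so no new data are needed, and SPSS can do all of it. The downside is that a linear trend loses power for non-linear patterns, including monotone steps by school stage. Reporting both results covers this.
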